### Adverse events

There are no known health or safety risks related to any aspect of the described study. There are no known risks for MRI and no sedation will be used. The principal researchers [name], [name] and [name] will review any adverse event or unintended effect detected.

### Data analysis and statistical considerations

When models involve brain structure and function data from one time point (either 30–32 or 40–42 weeks), standard regression models will be constructed; when models use data from both 30–32 and 40–42 weeks, mixed-effects models that take into account within-infant correlation will be used. Models will be constructed using standard principles; first univariable analyses will be used to identify variables significant at the *p* < 0.15 level and these variables then entered into multivariable models one-by-one, in decreasing order of significance. At each step the current model will be compared to previous models using the likelihood ratio test. Linear regression will be used for continuous outcomes (e.g. diffusion MRI measures of FA and MD); logistic regression for binary outcomes (e.g. disability/no disability); and multinomial logistic regression for categorical outcomes with > 2 categories (e.g. NSMDA categories of normal/suspect/abnormal). Results will be presented as effect estimates and 95 % confidence intervals. The sensitivity and specificity of the predictive assessment model will be determined based on diagnosis of disability using standard definitions. Perinatal, clinical, demographic and social characteristics will be included as covariables when appropriate. Analyses will be supervised by [name], a senior biostatistician at The University of Queensland.

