### Primary aims

In a prospective cohort study of infants born at ≤30 weeks, and a term reference group, this study aims:To examine the relationship between brain structure on structural and diffusion MRI, brain function on clinical measures of neurological, neuromotor and neurobehavioural performance, and perinatal risk factors at 30 and 40 weeks PMA.To determine whether brain structure and function at 30 weeks PMA predicts outcomes of brain structure and function at 40 weeks PMA, 3 months CA and 12 months CA.To evaluate the ability of structural and diffusion MRI and functional measures at 30 and 40 weeks PMA age to predict motor outcome at 3 months CA and motor, neurodevelopmental outcome and CP at 12 months CA.To evaluate the ability of perinatal variables and social risk (socio-economic status; SES) to predict severity of motor outcome and CP at 12 months CA.

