### Inclusion criteria

Infants born at ≤30 week’s gestation, who live within 200 km of the hospital to allow for follow up hospital appointments and home visits, and have English speaking families as there is insufficient funding for translators, are eligible for this study.

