### Perinatal data collection

An extensive record of the pregnancy, birth history, and neonatal course will be collected from the medical discharge summary. This will allow detailed description of the characteristics of the sample, allow comparison to outcomes establishing predictor variables, and to adjust for confounders.

A number of prenatal variables have been shown to impact short and long-term outcomes. Prolonged rupture of membranes, defined as spontaneous rupture of membranes ≥24 h before delivery is the most significant risk factor of a poor outcome among pregnancy history [94, 95]. Maternal antenatal corticosteroid administration reduces the risk of neonatal death and respiratory distress (complete course defined as more than 1 dose of steroids given, and 1st dose at more than 24 h and less than 8 days before birth) [94–96]. Evidence also exists for antenatal steroids protecting against cerebral haemorrhage [97]. The neuroprotective effect of magnesium sulphate administration reduces the risk of an outcome of CP (relative risk 0.68, 95 % confidence interval 0.54 to 0.87) [98]. Assisted conception is associated with adverse neurodevelopmental outcomes independent of prematurity, multiple pregnancy and gender for infants born between 22–26 weeks gestation [99]. Multiple birth status will be examined as the widely held view that singletons experience better outcomes than multiples has recently been challenged. In a population based study of *n* = 1473 born <29 weeks gestation, infants from multiple gestation pregnancies demonstrated comparable neurodevelopmental outcomes to singletons [100].

Birth history variables collected will include GA at birth, gender and birthweight. The risk of CP and adverse neurodevelopmental outcomes increases with decreasing GA at birth [101] and multiple studies report poorer outcomes for male infants [94, 102–104]. Intra uterine growth retardation (IUGR) can result in decreased cortical volume, poorer outcomes and increased risk of neonatal complications [105, 106] and babies that are small for gestational age (SGA) are at a higher risk of death, adverse neonatal outcomes and neurodevelopmental impairment [107]. Growth restriction in this study will be defined as a birth weight <10th percentile based on the Olsen growth curves.

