Socio-demographic information such as maternal and paternal education and occupation will be collected using a baseline parent questionnaire (see Additional file 1). Social and environmental factors may impact infant development, and low socio-economic status and parenting factors have been shown to adversely influence outcomes [120]. Social risk will be assessed using a score measuring six aspects of social status including: family structure, education of primary caregiver, occupation of primary income earner, employment status of primary income earner, language spoken at home and maternal age [116, 121, 122]. Each item will be scored between 0 and 2 for a total score of 12, with scores of 2 and above being considered high social risk in line with other research in this population [121, 122]. Higher social risk has been strongly associated with later behaviour problems, and independently predicts a lack of early intervention services [122, 123]. A recent systematic review found evidence that lower socio-economic status results in an additional risk of CP, over and above the risks conferred by prematurity or lower birthweight [124].

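### Siblings from multiple births can be co-enrolled but would be analysed as independent, so standard errors are modestly too small for predictors that siblings share, chiefly social risk and maternal/antenatal variables in aim 4

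*Protocol article*

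**What the plan says.** **Who can enter.** Inclusion rests on gestation, distance from the hospital and language: "Infants born at ≤30 week’s gestation, who live within 200 km of the hospital", with English-speaking families. The exclusion criteria cover only relevant congenital or chromosomal abnormality and contraindications to MRI. Nothing restricts the cohort to singletons or to one infant per family.

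**Multiples are expected.** Under Perinatal data collection: "Multiple birth status will be examined as the widely held view that singletons experience better outcomes than multiples has recently been challenged".

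**How correlation is handled.** Under Data analysis and statistical considerations, when brain structure and function data come from one time point, "standard regression models will be constructed". When both time points are used, the plan is for mixed-effects models "that take into account within-infant correlation". Linear, logistic and multinomial forms are named. Variables are screened at p < 0.15 and added one at a time with likelihood ratio tests. Perinatal and social characteristics may enter as covariables. No family or mother effect, GEE or cluster-robust variance is mentioned.

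**Where shared predictors matter.** Primary aim 4 is to "evaluate the ability of perinatal variables and social risk (socio-economic status; SES) to predict severity of motor outcome and CP" at 12 months. On the social predictor: "Social risk will be assessed using a score measuring six aspects of social status". All six items describe the household or the parents.

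**The concern.** Siblings of one pregnancy share the social risk score, maternal age, the antenatal exposures listed under Perinatal data collection (steroids, magnesium sulphate, assisted conception) and, in essence, gestational age. Their outcomes are likely to be positively correlated. Ordinary regression then counts two siblings as two independent pieces of information about a predictor that has only one value per family.

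A multiple-birth covariate changes the fitted mean for multiples; it leaves siblings' residuals correlated. An infant-level random effect links an infant's own two measurements and does not link one infant to a sibling.

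At stake are the intervals and p-values for the family-level predictors of a primary aim, and the model-building steps that use them. Such predictors would pass the p < 0.15 screen, and then the likelihood ratio comparison, somewhat too easily.

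**Working it through.** **The plan's own figure.** The article quantifies nothing about siblings. Its only calculation is the sample size: 50 % against 5 % with cerebral palsy, ratio 7.6:1, alpha 0.05, power 90 %, 69 infants (8 + 61). The pooled-variance two-proportion formula (two-sided, no continuity correction) gives 8.10 infants in the smaller group, 8.10 × 8.6 = 69.6 in total, and power 89.7 % at 8 and 61. The stated 69 reproduces with every infant treated as independent.

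**Inputs for the sibling effect.** The share *f* of infants in co-enrolled twin pairs and the sibling intraclass correlation are not in the document. Assumed ranges: *f* = 0.2 to 0.4, ICC = 0.3 to 0.7.

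**Family-level predictor, continuous outcome.** With pairs and singletons only, the mean sibling-set size per infant is (1 − f) × 1 + f × 2 = 1 + f, so

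design effect DE = 1 + f × ICC.

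The true standard error is √DE times the reported one, so the reported one is too small by 1 − 1/√DE. The true size of a nominal 5 % test is 2 × [1 − Φ(1.96/√DE)]; for the 0.15 screen, 1.44 replaces 1.96.

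| f | ICC | DE | √DE | Reported SE too small by | True size of 5 % test | True size of 15 % screen |
|---|---|---|---|---|---|---|
| 0.2 | 0.3 | 1.06 | 1.030 | 2.9 % | 5.7 % | 16.2 % |
| 0.3 | 0.5 | 1.15 | 1.072 | 6.7 % | 6.8 % | 18.0 % |
| 0.4 | 0.7 | 1.28 | 1.131 | 11.6 % | 8.3 % | 20.3 % |

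In the bottom row the true standard error is 13 % larger than reported, which is the same as the reported one being about 12 % too small. In the middle row, 80 infants carry the information of 80/1.15 ≈ 70 about a family-level predictor.

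**Which predictors are affected.** Ordinary linear regression was simulated with N = 80, f = 0.3–0.4 and ICC = 0.5–0.8 (a slightly higher ICC range than in the table):

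| Predictor's correlation between siblings | True SE / reported SE | True size of 5 % test |
|---|---|---|
| 1 (family-level) | 1.08–1.16 | 7.1–8.9 % |
| 0.5 | 1.03–1.06 | 5.7–6.6 % |
| 0 | about 1.00 | about 5 % |

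For a predictor that differs mainly within families the error could run the other way, with standard errors too large.

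**Binary cerebral palsy.** The sample-size assumptions imply (8 × 0.50 + 61 × 0.05)/69 = 7.05/69 ≈ 10 % with cerebral palsy. If the assumed ICC of 0.3–0.7 holds on a latent normal scale, the correlation between siblings' yes/no outcomes at that prevalence is about 0.13–0.41. Then DE = 1 + 0.2 × 0.13 = 1.03 up to 1 + 0.4 × 0.41 = 1.16; the reported standard error is about 1–7 % too small and the 5 % test runs at about 5.3–6.9 %.

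**The case against.** The strongest reply is that this is silence, not error. A condensed article may leave siblings to the full protocol or analysis plan, and within-infant correlation may be named only to contrast one-time-point with two-time-point models. That carries some weight, since the text nowhere states that siblings are independent. But it does fix the models: standard regression in one case, and one named source of correlation in the other. Followed as written, these treat siblings as independent.

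A reader might also infer more than the document supports:

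- **That twins and triplets are known to be enrolled.** The article refers to multiple birth status and gives no number. An infant may be a multiple without an enrolled sibling, because families are approached subject to medical stability and the neonatologist's approval. Co-enrolment is allowed and likely, but inferred.
- **That all standard errors are too small.** Aims 1 to 3 rest largely on infant-level MRI and clinical measures, and within aim 4 sex, birthweight, haemorrhage, sepsis and lung disease are recorded per infant. The full design effect applies to the family-level subset.
- **That the sample size fails.** The 69 compares infants by white matter abnormality, an infant-level finding. Nothing in the document supports applying the full family-level design effect to it.

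The objection that few cerebral palsy events make random intercepts hard to estimate stands, and it shapes the fix.

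**Conclusion.** The point holds for predictors shared by, or positively correlated between, co-enrolled siblings, chiefly the social risk score and the maternal and antenatal variables of aim 4. As written, the models give standard errors that are too small for these; predictors uncorrelated between siblings are barely touched. The direction follows from the design wherever siblings' outcomes are positively correlated. The size rests wholly on assumed values and is modest: for a family-level predictor of a continuous outcome, a design effect of 1.06–1.28, with the reported standard error about 3–12 % too small. It is less for cerebral palsy, and would be more if triplets were common. This should be corrected; it does not threaten the study as a whole.

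**What to change.** In Data analysis and statistical considerations, state that infants from one pregnancy form a cluster, and record a family identifier. Then:

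- **Two-time-point mixed models:** add a family (mother) random intercept, with infant nested in family.
- **Single-time-point regressions, and intervals for sensitivity and specificity:** use GEE or cluster-robust standard errors by family, with a small-sample correction.
- **Model building:** where robust errors are used, replace ordinary likelihood ratio tests with Wald or score tests that respect the clustering, including at the p < 0.15 screen.
- **Cerebral palsy:** where events are too few to estimate a random intercept, use the marginal (GEE or robust) form, or a sensitivity analysis with one infant per family.

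Report how many infants belong to co-enrolled sibling sets, so that readers can judge the effect.

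The cost is slightly wider intervals and a minor change to the model-building test. With about seven expected cerebral palsy cases, robust errors will themselves be imprecise, which is why the sensitivity analysis is worth keeping. No new assessments or design changes are needed.

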### Sample size

There are no data currently available to assess the relationship between MRI and clinical measures at 30 weeks PMA to predict motor outcome at 3 months CA and motor/neurodevelopmental outcome or CP at 12 months CA. Sample size calculations are based on a study investigating the ability of MRI at TEA, and the GMs assessment, to predict motor outcomes and CP at 12 months CA [6]. In a prospective cohort of infants born <30 weeks GA and in a total sample size of *n* = 86, MRI was classified as normal (*n* = 22), or with mild (*n* = 54), moderate (*n* = 6) or severe (*n* = 4) white matter abnormality (WMA) [93]. Infants with normal or mild WMA were grouped (*n* = 76), and infants with moderate and severe WMA were grouped (*n* = 10) [6]. We assume the same ratio (7.6 MRI normal or with mild/moderate WMA: 1 MRI with moderate/severe WMA) will be observed in this study. Of the *n* = 10 infants in the prior study that had moderate/severe WMA, *n* = 5 (50 %) developed CP [6]. If we assume that 5 % of infants with MRI normal or with mild/moderate WMA develop CP, then the study requires 69 infants to be recruited (8 with MRI with moderate/severe WMA and 61 with MRI normal or with mild/moderate WMA) in order to be able to reject the null hypothesis that the proportion of infants with CP in the two groups are equal with power = 90 %. The Type I error probability associated with this test of this null hypothesis is 0.05. In order to explore WMA earlier, at 30 weeks PMA, and its ability to predict CP at 12 months CA, an increase in the projected numbers will be required, and a further 15–20 % added to account for attrition. Consequently, the aim is to recruit a total sample size of 80 infants with full data sets.

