## Discussion

To our knowledge, this protocol describes the first study examining the clinical correlates of early advanced brain imaging and clinical measures at 30 weeks PMA to predict motor and neurodevelopmental outcomes at 3 and 12 months CA.

The results of this study will i) establish the relationships between early clinical measures, EEG, perinatal variables and nutrition and early advanced neuroimaging at 30 weeks PMA, ii) establish which components of brain structure and function most accurately predict neurodevelopmental, motor outcomes and CP at 3 and 12 months CA, iii) accurately identify infants at risk of adverse outcomes at an earlier stage, introducing an additional window of opportunity for intervention, iv) contribute to understanding brain development between 30 and 40 weeks PMA, v) and develop robust quantitative biomarkers of brain maturation, which can then be used in the research of interventions in this population.

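### Screening at p < 0.15 with one-by-one entry, on about 7 expected CP cases and dozens of candidates, is likely to overstate the accuracy of the CP prediction models

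*Protocol article*

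**What the plan says.** The section *Data analysis and statistical considerations* of the protocol article fixes the model-building rule. Each candidate is tested alone and kept if p < 0.15, with "these variables then entered into multivariable models one-by-one, in decreasing order of significance". Each step is compared with earlier models by likelihood ratio test. Binary outcomes use logistic regression. The section then states: "The sensitivity and specificity of the predictive assessment model will be determined based on diagnosis of disability using standard definitions".

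Prediction of CP at 12 months is among the *Primary aims* (third and fourth), and the *Sample size* section is built on CP. The *Discussion* expects the results to "establish which components of brain structure and function most accurately predict neurodevelopmental, motor outcomes and CP at 3 and 12 months CA", and to identify at-risk infants early enough to open a further window for intervention.

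**The concern.** Choosing predictors by significance and then measuring accuracy in the infants used to choose them favours whatever happened to separate cases from non-cases in that sample. The bias grows as events become fewer and candidates more numerous. Here the event count is very low and the list of measures is long, so a model of little or no real value can look useful. The study's main product is a statement of which early measures predict CP best. If that statement rests on inflated accuracy, it may not replicate, yet it could be used to decide which infants receive early intervention.

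**Working it through.** **1. The plan's own sample size.** The inputs are all in *Sample size*: CP risk 50 % with moderate/severe white matter abnormality (5 of 10 in the earlier cohort); "If we assume that 5 % of infants with MRI normal or with mild/moderate WMA develop CP"; a group ratio of 7.6 to 1; power 90 %; and "The Type I error probability associated with this test of this null hypothesis is 0.05" (sidedness is not given; two-sided reproduces the figure).

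Pooled risk p̄ = (0.50 + 7.6 × 0.05) / 8.6 = 0.1023.

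n₁ = [1.96 √(p̄(1 − p̄)(1 + 1/7.6)) + 1.2816 √(0.25 + 0.0475/7.6)]² / 0.45² = 8.10, and n₂ = 7.6 × 8.10 = 61.55. The total is 69.6 against the stated 69, and power at 8 + 61 is 0.897. The figure reproduces. It powers one two-group comparison, not a multivariable model.

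**2. Expected CP cases.** 8 × 0.50 + 61 × 0.05 = 4 + 3.05 = 7.05 in 69 infants. Scaled to 80: 80 × 7.05/69 = 8.2. If 15–20 % of 80 are lost: 6.5–7.0.

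**3. Candidates at 30 weeks**, counted from the measures sections:
- MRI: 4 tract metrics × at least 4 named pathways = 16, plus 2 injury classifications = 18.
- Clinical: 13 NNNS summary scores, HNNE, 3 Premie-Neuro subscales, GMs = 18.
- Perinatal: about 16, plus social risk = 17.

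The total is about 53, or 36 without perinatal and social variables. Cases per candidate: 7.05/53 = 0.13 to 8.2/53 = 0.15.

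**4. Screening alone.** Noise variables expected to pass p < 0.15: 0.15 × 20 = 3; × 30 = 4.5; × 40 = 6. The chance that at least one passes, 1 − 0.85^K, is 96 %, 99 % and 99.8 %.

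**5. Simulation of the stated rule on pure noise.** 69 infants, 7 cases, entry at likelihood ratio p < 0.05 (assumed). True AUC is 0.50. There are three sets of runs: all-continuous predictors (400 per setting), half binary (250–300 per setting), and one extending to 50 candidates. AUC, sensitivity and specificity are means over runs that select a model.

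| Candidates | Runs selecting a model | Apparent AUC | Sens/spec at best cut | All runs with AUC ≥ 0.80, where computed |
|---|---|---|---|---|
| 10 | 42–53 % | 0.75–0.78 | 0.89/0.59 | 15 % |
| 20 | 66–76 % | 0.79–0.82 | 0.84/0.77 to 0.88/0.68 | 36 % |
| 30 | 83–91 % | 0.84 | 0.87/0.79 to 0.90/0.73 | 60 % |
| 40 | 95 % | 0.87 | 0.92/0.78 | 75 % |
| 50, independent | 96 % | 0.90 | – | – |
| 53, correlated in blocks (0.2–0.6, assumed) | 92 % | 0.86 | 0.89/0.80 | 71 % |

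Applied to new infants, the same models have mean AUC 0.50.

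**6. Sensitivity to what the article does not state.**
- Entry level 0.15 instead of 0.05: AUC 0.84 (20 candidates) and 0.88 (30).
- Cut-off: at the CP prevalence, sensitivity is close to the best-cut value (0.84–0.87 with 20–40 candidates). At a predicted probability of 0.5 it stays below 0.5 (0.05–0.44 across settings).
- Wider endpoint, assumed 20–30 events in 80: AUC 0.68–0.73 with 20–30 candidates, and 0.75 with 53 correlated candidates and 20 events.

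**7. Does correction expose it?** With 30 noise candidates, repeating the whole selection inside stratified 7-fold cross-validation lowers mean AUC from 0.81 to 0.55 (Monte Carlo SE 0.02; runs or folds without a model counted as 0.50). Most of the optimism goes.

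**The case against.** Five points can fairly be made for the plan.

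*Endpoint.* The accuracy sentence refers to disability, not CP alone, and the *Background* gives 10–15 % CP plus a further 40–50 % with minor motor and behavioural difficulties. A wider endpoint could have many more events. This stands: the inflation is then smaller, though still present. CP remains a named outcome of the primary aims.

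*Size of the pool.* The article does not fix how many candidates enter one model. The third and fourth primary aims treat MRI and functional measures apart from perinatal and social ones, and the latter may enter only as covariables. This stands, and it is why a range is shown. Even one domain at 30 weeks supplies about 17–18 candidates, close to the 20-candidate row.

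*Validation.* A reader might infer that no correction or validation is planned. The documents do not support that. This is a condensed article, and internal validation, entry level and cut-off may sit in a fuller plan. That accuracy is measured in the same infants is itself inferred from there being a single preterm cohort. What the text does fix is the screening and entry rule.

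*Cut-off.* A reader might take sensitivities of 0.84–0.92 as what the study would report from noise. They require a cut-off at or near the best one, and none is stated. The AUC inflation does not depend on a cut-off.

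*Intervals.* The section promises effect estimates with 95 % confidence intervals. These convey imprecision; ordinary intervals from a selected model do not remove selection optimism.

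**Conclusion.** The concern holds as a likely and substantial overstatement of accuracy for CP, caused by a rule the article states rather than by a missing detail. On the plan's own assumptions there are about 7–8 CP cases. With 20 to about 50 noise candidates, apparent AUC averages 0.79–0.90 where the truth is 0.50.

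It would go too far to say that the plan will report good prediction from noise. With 10 candidates a model emerges in only about half of runs, and the AUC figures are conditional on one emerging. Nor does the simulation say that the real measures are noise: it shows how much apparent accuracy the procedure can create by itself. The figures are for logistic models and do not cover the linear or multinomial ones.

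The size rests on assumptions not in the article: entry at 0.05, the number and correlation of candidates, the cut-off, and the event count for disability.

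**What to change.** For the CP and disability models, replace the p < 0.15 screening and stepwise entry with either a very small predictor set named in advance for each time point, or penalised (ridge or LASSO) logistic regression. Even 2–3 predictors on 7 cases leaves only 7/3 = 2.3 to 7/2 = 3.5 events per predictor, so accuracy still needs correcting. Firth regression deals with small-sample bias and separation but does not select variables, so it is no substitute for the selection step.

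Report AUC, sensitivity and specificity corrected for optimism by a bootstrap or cross-validation that repeats every selection and cut-point step. Give exact confidence intervals; for example, 4 of 7 cases detected has a 95 % interval of 18–90 %. Define the disability endpoint and the cut-off rule, and describe the result as model development needing external validation.

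The cost is new wording in the analysis section, some computing, and less favourable reported accuracy. Recruitment, imaging and follow-up are unaffected.

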#### Neurosensory Motor Developmental Assessment (NSMDA)

The NSMDA is a discriminative and predictive, criterion-referenced test of gross and fine motor development [65, 169]. It examines gross and fine motor performance, neurological status, posture, balance and response to sensory input. The examiner observes and administers items and the test takes 10–30 min to complete. The results give a total score and a functional classification of motor development as normal, or with mild, moderate or severe problems of posture, movement and co-ordination. Assessment at 4 months predicts outcomes at 24 months with a sensitivity of 80 % and a specificity of 56 % [170]. Studies looking at the longer term predictive validity of the NSMDA, found assessment at 12 months had strong associations with motor and cognitive scores at 4 years [171], and NSMDA assessment at 8 months to have an 80 % sensitivity of motor outcomes at 11–13 years in extremely low birth weight infants with no apparent neurological deficit or CP [172]. The NSDMA will be used to classify each infant’s development as normal or as having mild, moderate, severe or profound motor dysfunction at 12 months CA.

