#### Alberta Infant Motor Scale (AIMS)

The AIMS is a discriminative, norm-referenced tool that tests gross motor skills through the components of weight bearing, posture and antigravity movements [162, 173]. The test involves observation of the infant in prone, supine, sitting and standing and is able to be completed in this study purely through observation during the Bayley III and NSMDA assessments with no additional handling. Normative data are based on a population of 2200 term infants from 0–18 months in Alberta, Canada [174], and when recently compared with a contemporary sample of 650 Canadian infants, found to still be relevant. Normative data for preterm infants has also been published with a sample of 800 infants born at ≤32 weeks from the Netherlands [175]. Raw scores are obtained with centile ranks and age equivalent growth scores available for term and preterm infants. The AIMS has high inter-rater reliability (ICC = .98 to .99) [176, 177], and intra-rater reliability (ICC = .97-.99) [177]. Concurrent validity with the Bayley II at 12 months CA in a cohort of preterm infants has been established (*r* = .90) [177]. Although the AIMS was not designed as a predictive tool, it has moderate to excellent predictive validity. In a sample of 164 preterm infants assessed at 8 months CA, the AIMS predicted motor outcomes at 18 months CA with a sensitivity 86.4 % and specificity 93 % [178]. The suitability of using the AIMS as a discriminative and predictive tool at 12 months CA in preterm infants has been supported by a clinimetric review of neuromotor measures for preterm infants in the first year of life [65]. The AIMS will be used to classify each infant’s development as normal or suspicious/abnormal at 12 months CA in this study.

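### The NSMDA grade has three conflicting category sets, and a multinomial model ignores its order, which probably costs power

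*Protocol article*

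**What the plan says.** The section on data analysis and statistical considerations gives one rule for every outcome with more than two categories: "multinomial logistic regression for categorical outcomes with > 2 categories (e.g. NSMDA categories of normal/suspect/abnormal". That makes three levels for the NSMDA.

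The NSMDA section gives two other sets. In general terms, the instrument yields a total score and "a functional classification of motor development as normal, or with mild, moderate or severe problems of posture, movement and co-ordination", which is four levels. For this study, each infant's development will be classed as "normal or as having mild, moderate, severe or profound motor dysfunction at 12 months CA", which is five.

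The word used for the middle level in the analysis section is not an NSMDA grade in the NSMDA section. The nearest wording belongs to another instrument: the AIMS section classes "development as normal or suspicious/abnormal at 12 months CA in this study".

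The fourth primary aim is to predict how severe the motor outcome is from perinatal and social variables.

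**The concern.** There are two linked problems.

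First, three definitions of a 12-month motor outcome stand side by side with no rule for getting from one to another. Until one is fixed, the cut-points could be chosen after the data are seen, and the number of coefficients in the model is unknown.

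Second, NSMDA grades are ordered by severity, and the fourth primary aim asks about severity. A multinomial model treats the grades as unordered labels. It returns K-1 contrasts per predictor (two for three levels, four for five) and no single severity effect, and it tests each predictor on K-1 degrees of freedom. The plan screens predictors at p < 0.15 and then builds models by likelihood ratio tests, so the extra degrees of freedom are paid for at both stages. The same rule covers the 12-month neurological examination, which is classed as normal, unspecified signs or abnormal.

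**Working it through.** **1. The plan's own figure.** The only power statement concerns CP by white matter group, 8 against 61 infants, with rates of 50 % and 5 %. With two-sided α = 0.05 (sidedness is not stated):
- pooled rate = (8×0.5 + 61×0.05)/69 = 7.05/69 = 0.102
- SE under the null = √[0.102×0.898×(1/8 + 1/61)] = 0.114
- SE under the alternative = √[0.25/8 + 0.0475/61] = 0.179
- z = (0.45 − 1.96×0.114)/0.179 = 1.27, so power = 0.897

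This matches the stated 90 %. It is a binary comparison and does not depend on the NSMDA model. No power is stated for any multinomial analysis.

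**2. Category sets side by side.**

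| Place | Levels | Coefficients per predictor, multinomial | Ordinal |
|---|---|---|---|
| Data analysis section | 3 | 2 | 1 |
| NSMDA section, general description | 4 | 3 | 1 |
| NSMDA section, use at 12 months | 5 | 4 | 1 |

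**3. Cost of the extra degrees of freedom.** Take an ordered effect with 80 % power on 1 df at α = 0.05. Its noncentrality is (1.96 + 0.8416)² = 7.85. Hold that fixed and spread it over more df:

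| df | Power at 0.05 | Chance of passing the p < 0.15 screen |
|---|---|---|
| 1 | 0.80 | 0.91 |
| 2 | 0.71 | 0.86 |
| 3 | 0.64 | 0.82 |
| 4 | 0.60 | 0.78 |

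**4. Simulation.** One standardised predictor, data generated with proportional odds true, likelihood ratio tests at 0.05, 600 data sets per setting. The grade shares and odds ratios are assumptions, because the article gives neither. The sample size is 80 as targeted, or 80×0.85 = 68 if 15 % are lost.

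| Shares (%) | OR per SD | n | Multinomial | Ordinal | Loss (points) |
|---|---|---|---|---|---|
| 60/25/15 | 2.0 | 68 | 0.697 | 0.810 | 11 |
| 60/25/15 | 2.0 | 80 | 0.767 | 0.853 | 9 |
| 75/15/10 | 2.0 | 68 | 0.535 | 0.635 | 10 |
| 75/15/10 | 2.0 | 80 | 0.662 | 0.755 | 9 |
| 60/25/15 | 1.8 | 68 | 0.553 | 0.670 | 12 |
| 75/15/10 | 1.8 | 68 | 0.448 | 0.513 | 7 |
| 55/30/8/4/3 | 2.0 | 68 | 0.653 | 0.825 | 17 |
| 55/30/8/4/3 | 2.0 | 80 | 0.702 | 0.862 | 16 |

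A separate run at n = 68 and odds ratio 2 gave 0.69 against 0.80 for three levels (11 points) and 0.62 against 0.76 for five (14 points). With no effect, rejection rates at n = 80 were 0.047 to 0.072 for the multinomial test and 0.047 to 0.058 for the ordinal test. The gap therefore does not come from a conservative multinomial test.

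**5. When proportional odds fails.** With three levels and cumulative log-odds slopes of 0.2 at one cut and 1.1 at the other (assumed), multinomial power was 0.82 and ordinal power 0.36. Under moderate departures the two were close.

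**6. Cell counts.** With three levels, take CP as a proxy for the worst level. The sample size inputs give 8×0.5 + 61×0.05 = 7.05 of 69. The Background's CP rate of 10–15 % gives 8 to 12 of 80. At n = 68 the chance that the smallest cell holds two or fewer is 0.1 to 3 % over the three-level shares tried. For four levels (assumed 55/30/10/5) it is 36 %. For five (55/30/8/4/3) it is 85 %, with about an 18 % chance of an empty cell.

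**The case against.** The strongest reply is that the power comparison favours the ordinal model by construction, because the data were generated with proportional odds. Nothing in the article supports that assumption. The Background separates CP from minor motor and behavioural difficulties, so a predictor of CP need not shift the boundary between normal and mildly affected infants by the same amount. This stands. It makes the loss conditional, and it means that an ordinal model without a check and fallback could do worse than the stated plan.

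A second reply is that the plan already allows a severity analysis: the NSMDA yields a total score, the Bayley III motor composite is continuous, and continuous outcomes go to linear regression. This stands in part. The article does not say that the NSMDA total score will be analysed, and it names the NSMDA grade as the example for the multinomial model.

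A third reply is that collapsing rules are commonly left to an analysis plan that is not shown. That would excuse silence. It does not excuse three incompatible category sets in one article.

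A reader might also infer that the stated analysis leaves near-empty cells and may not converge. The documents do not support this for the three-level version in the analysis section, where the worst cell holds about 7 of 69. It becomes a risk only if four or five grades are modelled, and how great a risk depends on shares that the article does not give. Nor would an ordinal model fill sparse cells; it only relies on them less.

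**Conclusion.** The contradiction in NSMDA categories is certain and must be reconciled. The model choice is a matter of efficiency and interpretation, not validity: multinomial regression is a legitimate analysis of ordered grades, and a reader who infers that its tests are invalid goes too far.

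If proportional odds roughly holds, ignoring the order costs about 7 to 12 points of power with three levels and 14 to 17 with five, at 68 to 80 infants. These figures rest on assumed shares, an odds ratio of 1.8 to 2 per SD and a single predictor. With moderate non-proportionality there is little or no loss, and with strong non-proportionality the multinomial model is the more powerful.

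The sample size of 69, and the sensitivity and specificity based on a disability diagnosis, do not depend on this model.

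The point might seem to extend to GMFCS level, but that is recorded only where CP is confirmed, which is about 7 infants on the article's own assumptions. That is too few for such a model.

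**What to change.** 1. Reconcile the NSMDA section and the data analysis section to one category set, and give a prespecified rule for collapsing sparse upper grades.
2. Use proportional-odds logistic regression for the NSMDA grade and for the three-level neurological examination. State how the assumption will be checked, and name the fallback: a partial proportional-odds or multinomial model.
3. Keep multinomial regression for outcomes whose categories have no order.
4. State that the NSMDA total score is also analysed as continuous by linear regression.

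The cost is wording only, with no new data or assessments. The downside is reliance on proportional odds, since a check of that assumption has limited power at this sample size. The fallback should therefore be written down in advance.
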